## Abstract

**Background:**

Patellofemoral pain (PFP) is a common musculoskeletal disorder resulting in anterior knee pain. Physiotherapy is the current standard treatment, while surgical intervention (tibial tubercle transfer [TTT]) is reserved for chronic cases when nonoperative treatment has failed. TTT can result in clinically meaningful improvement in patients with patellofemoral maltracking without instability. However, to date, no randomised controlled trials (RCT) have compared TTT combined with a physiotherapy (PT) programme to PT alone as the initial treatment for PFP.

**Methods:**

A single-centre nonblinded RCT in 40 patients with chronic PFP (> 1 year) and tibial tubercle-trochlear groove (TT-TG) > 15 mm will be randomised to either TTT followed by PT or to PT alone in a 1:1 ratio in a concealed manner. The primary outcome is knee pain at 18 weeks for the TTT group (6 weeks splint phase + 12 weeks PT) and at 12 weeks for the PT group, measured by the visual analog scale (VAS). Secondary outcomes include Patient-Reported Outcome Measures (PROMs) using the Kujala score, International Knee Documentation Committee (IKDC) ‘Subjective Knee Form’, Tegner Activity score and EuroQol 5D-5 L for quality of life. Range of motion (ROM) is measured using the decline step-down test (DSDT). Between-group differences will be analysed using multivariable linear regression analysis, while longitudinal differences will be assessed with linear mixed models for repeated measures. The difference in direct medical costs will also be assessed.

**Discussion:**

The REVITALISE study is the first randomised study to compare surgical intervention (TTT) followed by PT to PT alone in patients with chronic PFP. This study will generate level-1 evidence on the most effective treatment for chronic PFP, which can be integrated into the national guideline to aid orthopaedic surgeons and physiotherapists in their decision-making and ultimately improve our care for patients with chronic PFP.

**Trial registration:**

Study Identifier NCT06227806, registered on 26 Jan 2024 on ClinicalTrials.gov. The study underwent independent peer review and received approval from the ethical review board (number NL80956.091.22).

**Supplementary Information:**

The online version contains supplementary material available at 10.1186/s12891-024-08226-y.

## Introduction

### Background and rationale

Patellofemoral pain (PFP) is one of the most common forms of anterior knee pain, with a reported prevalence of 15–45% in physically active adolescents and adults, and it is more commonly diagnosed in women [1–3]. The symptoms are aggravated by activities involving loading the patellofemoral joint during weight-bearing on a flexed knee [4]. Additionally, psychological factors are influencing the experience of pain and are also related to physical activity [5]. A relatively large proportion of patients (40%) diagnosed with PFP continue to experience symptoms one to six years after diagnosis [6–9].

The treatment goals for PFP are to reduce pain, improve patellofemoral tracking and alignment, and return to the pre-injury level of activities. The conservative treatment of PFP with physiotherapy for the quadriceps and hip muscles as the cornerstone has shown varying degrees of success, from no difference [10, 11] to improvement [8, 12, 13]. To date, surgical intervention is not recommended in the international PFP consensus statement because high-level evidence about its effects is lacking [8]. In the Dutch guideline on ‘anterior knee pain’, a multidisciplinary stepped care treatment strategy model is incorporated, consisting of education and an exercise programme [14]. However, if symptoms persist after 12 weeks, the effect of further exercise therapy or surgery is unknown.

Carlson et al. [15] reported that the tibial tubercle-trochlear groove (TT-TG) distance was significantly greater in patients with PFP. In patients with patellar dislocation, a TT-TG > 15 mm is considered a clinically relevant anatomical substrate that negatively affects patellofemoral tracking and stability [15, 16]. According to a recent meta-analysis, tibial tubercle transfer (TTT) can lead to good results with clinically meaningful improvement in patients with patellofemoral maltracking without instability [17], while arthroscopy did not [18, 19]. It is considered a relatively safe procedure with a low complication rate [20, 21]. However, no randomised controlled trials (RCT) analysing the value of TTT or comparing TTT with physiotherapy for the treatment of chronic PFP have been published.

To further clarify the additional value of surgery in PFP, a RCT will be conducted to compare TTT in conjunction with a physiotherapy (PT) programme versus a PT alone in patients with chronic PFP and a TT-TG > 15 mm.

### Objectives

The primary objective of this study is to compare the between-group difference in knee pain over time for TTT followed by PT versus PT alone in patients aged 18–35 years with chronic PFP. We hypothesise that TTT combined with PT will result in a larger decrease in knee pain than PT alone.

Secondary objectives are to compare the between-group and longitudinal difference in change in (1) knee function, measured by validated Patient-Reported Outcome Measures (PROMs), (2) range of motion (ROM), (3) quality of life (QoL), (4) the functional limitations, and (5) the direct medical costs.

The results of this study can be used to develop and implement a better stepped-care treatment strategy for PFP and can be integrated into the national guideline for “anterior knee pain” [14].

## METHODS

### Study design and setting

A single-centre RCT. All patients will be recruited and included at the Orthopaedics Department of the Canisius Wilhelmina Hospital (CWZ), Nijmegen, the Netherlands. Eligible patients are randomised into two equal groups:

The TTT group: 20 PFP patients who will be treated with TTT at the hospital of randomisation, followed by a 12-week supervised PT protocol;The PT group: 20 PFP patients who will be treated with the same 12-week supervised PT protocol.

This study will be conducted according to the principles of the Declaration of Helsinki [22] and in accordance with the Medical Research Involving Human Subjects Act (WMO), Good Clinical Practice (GCP) and the General Data Protection Regulation. The study will also be carried out in accordance with local legal requirements. This study was approved by the independent Ethical Committee METC Oost-Nederland (protocol number NL80956.091.22) and was registered on ClinicalTrials.gov (study identifier NCT06227806). Written informed consent will be provided by each participant before the start of the study assessments or the intervention. This protocol adheres to the SPIRIT checklist items.

### Participants

Participants between 18 and 35 years of age with at least 12 months of PFP and a tibial tubercle trochlear groove (TT-TG) distance ≥ 15 mm on CT or MRI will be recruited at the CWZ hospital in Nijmegen, The Netherlands. PFP is defined as:

Pain around or behind the patella aggravated by at least one activity that loads the patellofemoral joint (e.g., squatting, running, or jumping);Pain during daily life activities, such as: standing for an extended period, walking, or walking upstairs or downstairs.

Participants will be excluded when one or more of the following exclusion criteria are met:

Previous knee surgery;Reported ligamentous or meniscal injuries of the knee;A history of patellar dislocation (i.e. patellar instability), based on a positive apprehension test by physical examination and/or signs of instability on MRI, such as injury or rupture of the medial patellofemoral ligament [23]. However, subjects with patellar subluxation are included in the study;Malrotational deformity of the lower extremity evident from physical examination;Disabling general illness;Other diagnosed knee injuries, either clinically (such as jumper’s knee) or radiologically (such as osteochondritis dissecans);Patients who cannot undergo surgery;Pregnancy;Patients with inability to complete follow-up or with limited understanding of the Dutch language.

### Patient recruitment

All eligible patients will be approached by their treating physician at the orthopaedic department of the CWZ, provided with adequate patient information, and handed out a patient information file (PIF). They will be instructed about the TTT, PT, and possibility to crossover after 12 weeks of the PT. After having had sufficient time (> 24 h) to reconsider participation, they will be contacted by a researcher to obtain approval and plan a baseline visit where participants will sign informed consent. Patients will also be asked for permission to approach them for future related research. A list of all eligible patients will be recorded in a screening log, including those that do not wish to participate, as well as the reason if provided.

### Randomisation

Patients will be enrolled in the study by the study coordinator in the orthopaedic department. All patients who consent to participate in the study and meet the inclusion criteria will be randomised. Randomisation will be performed by the study coordinator after consent is signed and baseline data is collected. Patients will be randomised to the TTT + PT: PT only in a 1:1 ratio. The randomisation process will be carried out using a computer-generated randomisation method in the Castor electronic data capture (EDC) system [24], in random blocks of 4. The exact randomisation algorithm is unknown to any of the investigators; hence, concealment of allocation is successful in all patients.

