### Blinding

Neither the treatment providers nor the study coordinator will be blinded due to the study design (with a blatant intervention).

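### The claim that concealment succeeds in all patients does not follow from the design: with one published block size of 4, anyone who knows it and keeps count can foresee on average a third of allocations

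*Protocol article*

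**What the plan says.** All of the following is in the protocol article.

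- **Randomisation, allocation scheme:** "Patients will be randomised to the TTT + PT: PT only in a 1:1 ratio", computer-generated in the Castor system "in random blocks of 4". No other block size is given and no stratification factor is named.
- **Randomisation, who acts:** "Patients will be enrolled in the study by the study coordinator in the orthopaedic department", and "Randomisation will be performed by the study coordinator after consent is signed and baseline data is collected". The section also says that all consenting patients who meet the inclusion criteria will be randomised.
- **Randomisation, the claim:** the section ends with "The exact randomisation algorithm is unknown to any of the investigators; hence, concealment of allocation is successful in all patients".
- **Patient recruitment:** the treating physician approaches eligible patients. More than 24 hours later a researcher contacts them and plans the baseline visit, where consent is signed. A screening log lists all eligible patients, including those who decline.
- **Blinding:** staff know the arm of each treated patient, since the text says "Neither the treatment providers nor the study coordinator will be blinded due to the study design".
- **Study design and setting:** there is one site, given as "A single-centre RCT".
- **Trial status:** recruitment was open when the article was written and was expected to end on 24 October 2025.

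**The concern.** Concealment of allocation means that nobody who decides whether or when a patient enters can know the next assignment. Hiding the list is necessary for that, but it is not enough. With 1:1 allocation in blocks of one fixed size, the hidden list can be partly reconstructed from the block size and the assignments already made. The article gives the block size, and surgery versus no surgery is visible to everyone involved. The coordinator who carries out every randomisation has necessarily seen all earlier ones.

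At stake is selection before randomisation: who is approached, when the baseline visit is planned, and which of two waiting patients is entered first. The primary outcome is self-reported pain in an open trial of 20 patients per arm. The primary model adjusts for baseline VAS and sex. Selection on motivation or on expectation of surgery would not be fully captured by those two covariates.

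**Working it through.** The article gives no figure for predictability, so there is none to reproduce.

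**Inputs**
- Block size 4 and ratio 1:1, so two patients per arm in each block (Randomisation).
- 40 patients (Abstract, Methods), so 40 / 4 = 10 blocks.
- One sequence to follow: one centre (Study design and setting) and no stratification stated.
- Reading adopted: the stated scheme means randomly permuted blocks of fixed size 4, because only one size is given.

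**Step 1. Allocations known with certainty**

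An allocation is certain once one arm has used both its places in the block. There are 4! / (2! × 2!) = 6 equally likely orders:

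| Orders | Certain positions | Certain per block |
|---|---|---|
| AABB, BBAA | 3 and 4 | 2 |
| ABAB, ABBA, BAAB, BABA | 4 | 1 |

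- Expected number per block = (2 × 2 + 4 × 1) / 6 = 8/6 = 1.33.
- Share = 1.33 / 4 = 33.3%.
- Chance of certainty by position: 0, 0, 1/3, 1.
- Over 10 blocks: 10 × 1.33 = 13.3 of 40. The total is 10 + Binomial(10, 1/3), so it lies between 10 and 20, with a central 95% range of 11 to 16.

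**Step 2. Best guessing**

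Always guess the arm with more places left in the block, and toss a coin when they are equal. The chance of being right by position is 1/2, 2/3, 2/3 and 1. The mean is (1/2 + 2/3 + 2/3 + 1) / 4 = 17/24 = 70.8%, against 50% with simple randomisation.

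**Step 3. What varying block sizes would change**

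This was simulated for 40 patients with block sizes drawn with equal probability. The observer knows the set of possible sizes and all past allocations, but not the size of each block.

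| Scheme | Certain | Best guess correct |
|---|---|---|
| Fixed 4 | 33.3% | 70.8% |
| Random 2, 4, 6 | 3.9% | 70.0% |
| Random 4, 6 | about 5.5% | 68.9% |

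A larger fixed block would help less: if its size is known, 25% (size 6) or 20% (size 8) of allocations remain certain.

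Varying the sizes therefore removes most of the certainty but hardly touches guessing. Guessing the arm that is behind needs no knowledge of block size and works with any scheme of small balanced blocks.

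**Step 4. Balance under the varying scheme**

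All blocks are of even size and 40 is even, so the sequence can stop only after 2 or 4 patients of an unfinished block. The arms can then differ by at most 2, provided the change is made at the end of a completed block of 4.

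**The case against.** **The safeguards in the plan are real.** The list is computer-generated and hidden. Consent and baseline data precede randomisation. All consenting patients who meet the inclusion criteria are to be randomised, approach and consent are separated in time, and the screening log makes selective enrolment partly auditable. This stands. These steps make it harder to match a patient to a foreseen slot, but they do not stop the slot from being foreseen, and treatment providers are unblinded too.

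**The one third is conditional.** It requires that the person recruiting knows the block size and keeps count. The article says that the exact algorithm is unknown to the investigators, and it does not say that the coordinator knew the size before publication. It shows only that its authors did. Nor does it say how many patients had been randomised by then. This stands: about 13 of 40 applies only if the size was known from the first patient.

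**Blocks of 4 have a purpose.** They keep a 40-patient trial balanced. That is a fair reason for small blocks, but not for a single disclosed size.

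**Stronger readings that the text does not support.** A reader might infer that a third of allocations were in fact foreseen, or that enrolment was manipulated. Nothing in the document shows either. A reader might also take the 71% guessing rate as harm caused by the fixed size; Step 3 shows that it is not.

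**Conclusion.** The concern holds in a limited form. The inference from an unknown algorithm to successful concealment in every patient is wrong as written, because the same section gives what is needed to deduce some allocations. The statement also reports success while recruitment was still open.

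The size is 33% of allocations foreseeable with certainty, for someone who knows the block size and tracks allocations. Three assumptions carry this:

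- The blocks are of fixed size 4. If sizes in fact varied, the share is much lower, but the text then needs correcting for that reason.
- There is no stratification. Strata would need separate tracking, but the share per completed block would stay at one third.
- For the total of about 13, the block size is known throughout.

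The defect is worth correcting but does not invalidate the trial. Selection bias is possible and has not been shown.

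**What to change.** **For patients not yet randomised.** Have someone outside the recruiting team set randomly varying block sizes in the randomisation system, for example 2, 4 and 6, starting at the end of a completed block. Do not disclose the sizes to site staff or publish them until recruitment has closed. This lowers certain allocations from 33% to about 4%; best guessing stays near 70%, and the text should not suggest otherwise.

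**In any case, including if recruitment has closed.** Replace the sentence on successful concealment with a description of the procedure: computer allocation in Castor, released after consent and baseline data, with blocks of 4 for patients already randomised. State the residual predictability as a limitation.

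**Cost.** The arms may differ by 2 patients at 40. An amendment must be written and then filed or reported, as the Protocol amendments section requires. Someone independent of recruitment is needed to set the scheme. The article does not say whether the system allows a change of block sizes mid-trial, so this must be checked. The benefit reaches only patients still to be randomised, and their number is not given. Moving consent and baseline data ahead of allocation needs no change, because the plan already does this.

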### Blinding

Neither the treatment providers nor the study coordinator will be blinded due to the study design (with a blatant intervention).

#### Physiotherapy (PT) programme

This will start as soon as possible in the PT group and after the splint phase in the TTT group; the PT group will not wear a splint. The PT will consist of three levels and will be supervised by a physiotherapist. According to predefined criteria, the physiotherapist decides whether a patient can step onto the next level within the PT. The PT consists of flexibility, neuromuscular coordination, and strength exercises for the quadriceps and hip muscles. The PT is developed by a team of experienced physiotherapists who are specialised in treating patients with PFP and based upon the most recent physiotherapeutic insights [8]. In addition to training, education about PFP is incorporated into the PT according to the most recent insights regarding pain mechanisms [26, 27]. Physiotherapists who participate as self-chosen treating health care professionals by patients will be requested to follow an instructional video developed by the REVITALISE study team. Additionally, the three levels of exercise of the PT programme are available on the Physitrack^®^ tool for both participating physiotherapists and patients with PFP to improve exercise adherence and support clinical decision-making. In total, there will be 12 sessions with the physiotherapist. In the first three weeks of the PT, patients visit the physiotherapist twice a week. This will occur once a week from week 3 to week 6. This will occur every other week from week 6 to week 12. However, the treating physiotherapist may increase or decrease the number of appointments if needed. Additionally, the physiotherapist may adjust the exercises, sets, repetitions, weight and duration of loading tailoring to the specific needs of the patient. Since it is our intention that the PT is adjusted to the needs of each individual patient, the exact adherence and deviations to the protocol will not be monitored specifically. However, if necessary, we will consult with the treating physiotherapist in case the patient is not compliant. Moreover, the physiotherapist will be contacted by the study coordinator at the end of the PT to inquire about possible feedback on the PT and patient adherence and progression. The PT is included in the supplementary material (Supplementary file 1), which contains more detailed information and instructions.

#### TTT and PT versus PT only

The study involves four outpatient visits (at inclusion/randomisation, 6 weeks after the start of the intervention, after 12 (PT group)/18 weeks (surgery + PT group), and after 26 weeks in both groups). A physical examination will take place at every outpatient visit, with the addition of the decline step-down test (DSDT) at baseline and 12/18 weeks after randomisation. Patients will complete online questionnaires at every outpatient visit and 12 months after randomisation.

After randomisation, patients will either have a TTT (treatment group) or start with the PT (control group). From 12 weeks, there will be the possibility to crossover from the PT group to surgery if the symptoms do not improve. The criteria for this are a persisting high level of pain and patient-reported lack of effect of the PT. In that case, surgery will be performed within 2 weeks. Participants will then follow the same protocol as the TTT group, including the PT programme, surveys, and physical measurements.

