### Outcomes

#### Primary outcome

The main study parameter will be the between-group difference in activity-related knee pain at 12 weeks after PT in both groups, measured with the 10 cm VAS-scale. The point in time is different for the two groups, since there is a 6 week splint phase incorporated in the TTT group. Thus, knee pain will assessed at week 18 in the TTT group (6 weeks for the TTT and splint + 12 weeks of PT) and at week 12 in PT group. To compare both treatments as reliably as possible, we opted to not set this outcome measure further in time, due to the possibility for cross-over from the PT group to the TTT group. Furthermore, we expect that a plateau phase of pain will be reached within this period. The mean from the two VAS pain scores in week 12 (PT group) and 18 (TTT group) by the weekly questionnaire and outpatient visit will be used to account for variance in pain levels. Participants will assess the maximum pain they had felt during the previous 7 days when participating in activities of daily living such as ascending stairs, descending stairs and standing up from a sitting position. The 10-cm VAS is a valid and responsive tool for evaluating overall pain in patients with PFP [28]. A minimal clinically important difference (MCID) of 2 cm or 20% has been reported to reflect real changes in a patient’s symptoms [28].

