## Discussion

The REVITALISE study is the first RCT to compare surgical intervention followed by PT to PT alone in patients with chronic PFP. This study’s results will gain insight into the most effective treatment for patients with chronic PFP and will enhance our treatment of this high burden disease with currently a high variability of provided care [14]. This variation seems to be not or weakly associated with patient characteristics, elucidating the need for a more standardised approach to prevent over- or under treatment. The study will answer the question whether patients receiving TTT followed by PT have less pain and better functional outcomes than those receiving PT alone. In addition to measuring the effectiveness of TTT plus PT versus PT alone, a range of other outcomes will be assessed (e.g., physical function, complications, direct medical costs), to provide a broader view of the effect of both treatments.

The strengths of the study include the randomised controlled design supported with multiple involved professions. Physiotherapists are involved in the design of the PT. Orthopaedic surgeons are involved in the TTT protocol. Since this is a single-centre study, little or no variation in surgical technique is expected.

This study has several limitations. First, the crossover design potentially affects long-term (i.e., > 12 weeks) comparisons of the groups, as well as induces bias in cases where patients become less motivated to follow physiotherapy. However, as the primary analysis is according to the intention-to-treat principles, we do not expect this to have a major impact. Second, at the time of presentation at the hospitals, patients will have had different treatments, i.e., the care given by the family physician, the outpatient physiotherapist, or other involved professionals. In our physiotherapy programme, special care is given to education of the patient about PFP, as well as a focus on building balance and strength in multiple muscle groups, not only the quadriceps. Third, for logistical reasons, it is not possible for all participants to receive physiotherapy from the same physiotherapist. To limit protocol variations, we will contact each physiotherapist to explain the research design, the PT, and the need to adhere to this programme. Simultaneously, the physiotherapist should tailor the programme to the participants, as their individual needs and limitations are always the highest priority.

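### The PT arm's unblinded week-12 pain score is taken just as crossover to surgery opens on patient-reported pain, which can bias the primary comparison toward TTT

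*Protocol article*

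**What the plan says.** Under Patient recruitment, patients are briefed before consent: "They will be instructed about the TTT, PT, and possibility to crossover after 12 weeks of the PT".

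The section TTT and PT versus PT only sets the crossover rule. "From 12 weeks, there will be the possibility to crossover from the PT group to surgery if the symptoms do not improve". On the grounds, it says: "The criteria for this are a persisting high level of pain and patient-reported lack of effect of the PT". On timing: "In that case, surgery will be performed within 2 weeks".

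The Primary outcome section builds the endpoint from "The mean from the two VAS pain scores in week 12 (PT group) and 18 (TTT group) by the weekly questionnaire and outpatient visit". The rating is a recall of worst pain: "Participants will assess the maximum pain they had felt during the previous 7 days". The same section explains the timing: "we opted to not set this outcome measure further in time, due to the possibility for cross-over from the PT group".

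The abstract describes the trial as nonblinded, and the Blinding section confirms this for treatment providers and the study coordinator.

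The Discussion lists crossover as a limitation. It says that crossover may affect comparisons beyond 12 weeks, "as well as induces bias in cases where patients become less motivated to follow physiotherapy", and then expects no major impact because the primary analysis follows intention-to-treat.

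**The concern.** Setting the endpoint before crossover surgery can take place keeps that surgery out of the primary comparison. It also puts the PT arm's rating at the moment when a report of high pain and no benefit opens the way to an operation. A PT patient who hoped for surgery has something to gain from a high score, and a TTT patient does not.

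The distortion would raise PT scores and so widen the difference in the direction of the study hypothesis. The outcome is a self-rated recall by patients who know their treatment, so nothing in the measurement itself resists it. At stake is the reading of a positive primary result in a trial meant to inform a national guideline.

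**Working it through.** **1. Do the rating and the crossover criterion coincide?**

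| | Primary outcome, PT arm | Crossover criterion, PT arm |
|---|---|---|
| Construct | Activity-related knee pain, VAS | Persisting high pain plus perceived lack of effect |
| Reporter | Patient | Lack of effect: patient. Pain: no instrument or assessor named |
| Time | Week 12, weekly questionnaire and visit | From week 12 |
| Known to the patient | Yes, nonblinded | Yes, told before consent |

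Construct and time match, and so does the reporter, taking the pain criterion to rest on what the patient says. That the same VAS score is used for both is not stated. The TTT arm has no corresponding contingency at week 18.

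**2. Do the planned analyses deal with it?**

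- Intention-to-treat decides which group a patient is analysed in. The possible distortion is in a score recorded before anyone crosses over, so it stays.
- Adjustment for baseline VAS and sex (Primary endpoint section) does not touch a shift that arises only at week 12.
- The per-protocol analysis drops PT patients who crossed over. They are selected partly for high pain, so it brings in an error in the other direction and does not correct this one.

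**3. The plan's own sample size, reproduced.** Inputs from the Sample size section: difference 2, SD 2.0, two-sided alpha 0.05, power 0.8.

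n per group = 2 × (1.960 + 0.842)² × 2.0² / 2² = 15.7, so 16. With 20% loss: 16 / 0.8 = 20. Both agree with the protocol. (An exact t-test calculation gives 16.7, so 17; this is not at issue here.)

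**4. Possible size.** Assume a share f of PT patients over-report by b cm. Neither f nor b is in the document.

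Bias = f × b

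- f = 0.3, b = 1: 0.3 cm; 0.3 / 2 = 15% of the target difference
- f = 0.5, b = 2: 1.0 cm; 1.0 / 2 = 50% of the target difference

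**5. Effect on the error rate, with no true difference.** An unadjusted t-test is used as a simplification. Over-reporting by only some patients adds variance f(1 − f)b² in the PT arm.

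SD in PT arm = √(4 + f(1 − f)b²)

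Pooled SD = √[(4 + SD²) / 2], where SD is that of the PT arm

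Noncentrality = f × b / (pooled SD × √(2/n))

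For f = 0.5, b = 2, n = 16: SD in PT arm = √5 = 2.236; pooled SD = √4.5 = 2.121; noncentrality = 1.0 / (2.121 × 0.354) = 1.33, with 30 degrees of freedom.

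| f | b (cm) | Bias (cm) | False significance favouring TTT, n = 16 | n = 20 |
|---|---|---|---|---|
| 0 | – | 0 | 2.5% | 2.5% |
| 0.3 | 1 | 0.3 | 6.0% | 6.6% |
| 0.5 | 1 | 0.5 | 9.9% | 11.5% |
| 0.5 | 2 | 1.0 | 25.2% | 30.6% |

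**The case against.** The strongest reply is that the link is inferred. A reader might conclude that the week-12 VAS is itself the evidence that grants surgery, so that a patient obtains the operation by scoring high. The protocol does not say so. It requires persisting high pain together with perceived lack of effect, names no instrument or cut-off, and opens crossover from week 12 without tying it to one score. This stands, and limits the point to a coincidence of construct, reporter and time.

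A reader might also take the Discussion to claim that intention-to-treat removes reporting bias. It does not. Its reassurance concerns later comparisons and motivation for physiotherapy, and is worded as an expectation. The fair criticism is that this mechanism is left out.

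Existing provisions help in part. Half of the primary score comes from a weekly questionnaire sent by email, and visit questionnaires are already online. VAS over time, including the weekly scores, is a secondary outcome modelled longitudinally, and individual trajectories will be plotted. A jump at week 12 could be seen there, so it would be too strong to say that a positive result could never be examined for anticipatory reporting. But none of these gives a treatment estimate from ratings made before week 12, or looks separately at patients who then cross over.

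The order of rating and consultation may be set out in the full protocol, which is not shown. Its absence from the article is therefore not counted as an error. What counts is the design as described: the timing, the criterion and the prior disclosure.

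Finally, the VAS section notes that recovery from surgery may still affect TTT scores at week 18. If that raises them, it works against TTT, so the net direction of all influences together is open. It does not cancel a one-sided incentive in the PT arm.

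**Conclusion.** The point holds as a directional risk to the primary outcome. PT patients who want surgery have an incentive to report high pain in week 12, TTT patients have none, and the planned analyses do not correct for it. The direction of this mechanism, toward TTT, follows from the text.

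The size does not. The 0.3 to 1.0 cm range rests wholly on the assumed 30 to 50% of PT patients over-reporting by 1 to 2 cm. The error rates above also assume no true difference, SD 2.0 and an unadjusted test. They show that modest over-reporting would matter in a trial of this size, not that it will occur. It would go too far to call the bias established. No stated figure is wrong. This is a worthwhile improvement at low cost.

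**What to change.** Leave the clinical crossover criteria unchanged and separate them from outcome measurement:

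1. In both arms, have both VAS scores (week 12 for PT, week 18 for TTT) completed online and locked in the EDC before the visit consultation and before any talk of crossover.
2. State in the protocol and the patient information that study VAS scores are not shown to the surgeon and are not used in the crossover decision.
3. Prespecify a supportive analysis: the primary model with the mean weekly VAS of PT weeks 9 to 11 as outcome in both arms. Also report the change from weeks 9 to 11 to week 12 in PT patients who then cross over. Both go beyond the longitudinal model and plots already planned.
4. Add to the Discussion that intention-to-treat does not address differential outcome reporting before crossover.

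Cost: changes of wording in the protocol and patient information, an EDC setting, and one supportive analysis on weekly scores already being collected. The surgeon has to ask about pain separately, so the incentive is reduced, not removed. Weeks 9 to 11 reflect slightly less physiotherapy and may already carry some anticipation, so that analysis supports the primary one and does not replace it.
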